### Experimental procedures

Figure 2 displays the sequence of the experiment. The evaluations will be performed with the patient sitting comfortably in a chair with both feet flat on the floor, hips and knees at flexed at 90°, buttocks positioned against the back of the chair and treated shoulder unclothed. Data on pain (numerical rating scale and pain area) and cervical range of motion data will be collected at baseline (EV1).

**Figure 2 Fig2:**
[figure not shown]
**Flow sequence diagram of data recording.** (EV1, pain and cervical range of motion evaluation; EV2, Second pain and cervical range of motion evaluation, EV3, Third pain and cervical range of motion evaluation; EV4, Fourth pain and cervical range of motion evaluation; EMG-1, First electromyographic evaluation ; EMG-2, Second electromyographic evaluation; ROM, Range of motion; EMG, Electromyography; MVC, Maximal voluntary contraction).

Disposable electrodes will be attached for the collection of the sEMG signal in the upper trapezius muscle treated with acupuncture. Straps will be hung from the shoulders and connected in front and back by another strap with Velcro® to allow adjustments for the chest size of each individual. The ipsilateral strap to the shoulder on which the sEMG signal will be read will be attached to a load cell (EMG System do Brazil Ltda, São José dos Campos, São Paulo, Brazil) connected to a support attached to the chair (Figure 3). The strap on the contralateral shoulder will be attached directly to the chair. The straps will be individually adjusted and the volunteer will be instructed to raise the shoulder to be analyzed in maximum voluntary contraction (MVC) for five seconds, with a three-minute rest interval between readings.

**Figure 3 Fig3:**
[figure not shown]
**Details of experimental setup.** Two straps over the acromion -one attached directly to the chair and one attached to the support of a load cell **(A)**; Force and electromyography activity (**(B)** surface electrode) of the upper trapezius muscle will be measured simultaneously during shoulder elevation movements. Feedback will be provided from the projection of a 20-inch screen on a white wall in front of the subject.

The maximum value in Newtons (N) will be considered the MVC. After three minutes of rest following the last MVC, the first sEMG signal (EMG-1) will be collected. The volunteer will be instructed to perform a ‘step contraction’, consisting of five force levels (10, 15, 20, 25 and 30% MVC). To investigate possible myoelectric manifestations of fatigue, a repetition of the third step (20% MVC) will be added as the sixth step to determine differences in the sEMG variables between these two steps [22]. Contraction time will be 11 seconds for each force level. Feedback of the step contraction will be provided from the projection of a 20-inch screen on a white wall in front of the subject. All participants will receive training prior to the shoulder elevations, based on the previously determined force levels.

New evaluations of pain and cervical range of motion (EV2) will be performed after one minute of rest. Acupuncture will then be performed, with the needles remaining inserted for 30 minutes. After the removal of the needles, further evaluations of pain and cervical range of motion will be performed (EV3), followed by a second EMG reading (EMG-2) in the same manner as performed during EMG-1. A fourth evaluation of pain and cervical range of motion (EV4) will be performed after two minutes of rest.

### Electromyography signal processing

For the analysis of the sEMG signal, the first second of each step (considered as a transition time between force levels) will be discarded and the subsequent 10 seconds will be divided into one-second windows. The root mean square (RMS) and median frequency (MDF) of the power spectrum will be calculated for each window. All EMG signals will be processed performing specific routines carried out in the Matlab program, version 7.1 (MathWorks Inc., Natick, Massachusetts, United States).

### Sample size calculation

The sample size was calculated considering α = 0.05 (5% chance of type one error) and 1-β = 0.99 (% of power of the sample), and data on the amplitude of the EMG signal in the study by Chou *et al*. [26]. The values used were those described by Chou et al. [26] in the period prior to acupuncture (21.3 ± 9.5 μV) and after three minutes of needle manipulation in the acupoints TE-5 and LI-11 (9.5 ± 3.5 μV). The minimum number for each group was determined to be 12 individuals (total = 24).

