## Methods/Design

### Overview of research design

A randomized, single-blind, sham-controlled, crossover clinical trial will be carried out. The crossover design will be used to exclude the potential interference of individual differences. Figure 1 displays the flow of the study.

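### The stated 99% power comes from a one-treatment before/after amplitude drop and does not describe the real-versus-sham contrast that the crossover is built to make

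*Protocol article*

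**What the plan says.** The Sample size calculation section gives the error rates ("The sample size was calculated considering α = 0.05 (5% chance of type one error) and 1-β = 0.99") and two amplitude summaries from one cited study. One was taken "in the period prior to acupuncture (21.3 ± 9.5 μV"), the other "after three minutes of needle manipulation in the acupoints TE-5 and LI-11 (9.5 ± 3.5 μV"). It concludes: "The minimum number for each group was determined to be 12 individuals (total = 24"). It names no test, sidedness, pre/post correlation, SD of change or sham value.

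The Overview of research design section describes the trial thus: "A randomized, single-blind, sham-controlled, crossover clinical trial will be carried out". Under Randomization and blinding, each subject receives tACP and sACP in random order, six subjects per order in each group.

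Under Experimental procedures, the sequence after EMG-1 and EV2 is: "Acupuncture will then be performed, with the needles remaining inserted for 30 minutes". The needles are then removed, EV3 is done, and only then is EMG-2 recorded, during step contractions at 10 to 30% MVC.

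The Data analysis section regresses the EMG variables on force within each individual. It compares the slopes between EMG-1 and EMG-2 with a mixed linear model and names no treatment term.

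**The concern.** A power figure belongs to one comparison of one variable. Here the comparison behind the 0.99 differs from the trial's in three ways.

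- **Contrast.** The inputs describe change under one treatment. Random order, a sham and a wash-out serve the comparison of tACP with sACP.
- **Timing.** The external second value follows three minutes of manipulation. EMG-2 follows 30 minutes of needling, needle removal and another evaluation.
- **Variable.** The inputs are amplitudes in μV. The planned EMG comparison uses slopes on force, and no SD for a slope is given.

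If 0.99 stands as the trial's power, a non-significant tACP-sACP difference could be read as strong evidence that the acupoints do nothing. With 12 subjects per group and even a moderate sham response, that reading could be badly wrong.

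**Working it through.** **Inputs from the Sample size calculation section.** Means 21.3 and 9.5 μV, so Δ = 21.3 − 9.5 = 11.8 μV; SDs 9.5 and 3.5 μV; α = 0.05; power 0.99; n = 12 per group.

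**Step 1: where 12 can come from.** For a paired comparison with pre/post correlation r:

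SD_change = √(9.5² + 3.5² − 2·r·9.5·3.5), and dz = 11.8 / SD_change.

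Two-sided paired t-test (noncentral t):

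| r (assumed) | SD_change | dz | power at n = 12 | n for 99% |
|---|---|---|---|---|
| 0 | 10.12 | 1.166 | 95.6% | 16 |
| 0.3 | 9.09 | 1.299 | 98.3% | 14 |
| 0.5 | 8.32 | 1.418 | 99.4% | 12 |

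This test gives exactly 12 for r of about 0.42 to 0.53.

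Other routes:
- Two independent means, pooled SD = √((9.5² + 3.5²)/2) = 7.16, d = 11.8/7.16 = 1.648. The one-sided normal formula gives n = 2(1.645 + 2.326)²/1.648² = 11.6, so 12, with no correlation needed.
- The same formula two-sided gives 14. The two-sample t-test gives 15 per group two-sided (power 97.1% at 12) and 13 one-sided.
- A one-sided paired t-test gives 12 at r = 0.2.

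So the plan's figure is reproducible, but the article does not say by which route.

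**Step 2: power for tACP versus sACP.** The documents give no sham data, so these are assumptions: the external drop applies to tACP; sACP produces a fraction f of it; SD_change is the same under both treatments; the two changes in a subject correlate at ρ; n = 12; two-sided 5%; 10 degrees of freedom (two order groups of six).

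SD_diff = SD_change·√(2(1 − ρ)), effect = 11.8·(1 − f).

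| r | ρ | SD_diff (μV) | f = 0 | f = 0.25 | f = 0.5 |
|---|---|---|---|---|---|
| 0 | 0 | 14.32 | 73% | 49% | 25% |
| 0 | 0.5 | 10.12 | 95% | 78% | 45% |
| 0.5 | 0 | 11.77 | 88% | 65% | 35% |
| 0.5 | 0.3 | 9.85 | 96% | 80% | 47% |
| 0.5 | 0.5 | 8.32 | 99% | 91% | 60% |

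Within this grid, 99% is reached only with an inert sham and r = ρ = 0.5. Beyond it, an inert sham with r = 0.5 gives 99.8% at ρ = 0.6. A quarter-size sham response with r = 0.5 gives 98.9% at ρ = 0.7 and passes 99% at ρ = 0.8.

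**Step 3: what 12 subjects can detect.** On the same 10 degrees of freedom, the detectable effect in SDs of the within-subject difference is about 0.90 at 80% power, 1.04 at 90% and 1.38 at 99%. On the amplitude scale, 0.90 SD is 0.90 × 8.32 = 7.5 μV to 0.90 × 14.32 = 12.9 μV over the range of SD_diff above. No equivalent can be computed for slopes.

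**The case against.** The strongest reply is that the written analysis is itself a before/after comparison. The Data analysis section compares EMG-1 with EMG-2 and says this will show whether the acupoints act on the muscle, so a before/after sample size matches it in form. That stands as far as it goes: the need for a tACP-sACP contrast follows from the design, not from a named model term. It does not rescue the figure, because even the written comparison is of slopes and the 0.99 was computed on amplitudes.

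Stronger readings are tempting, and the documents do not support them:

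- **That 12 cannot be obtained from the stated figures.** It can, by at least the routes in Step 1. What is missing is the test, the sidedness and the correlation. An article may leave these to a fuller document, so their absence alone would be a small matter.
- **That real-versus-sham power is necessarily below 99%.** This depends on quantities the documents do not give. With an inert sham and correlations of about 0.5 or more, it equals or exceeds 99%. The low values depend on an assumed sham response.
- **That the external second reading was taken with the needles still in place.** The article says only "after three minutes of needle manipulation in the acupoints TE-5 and LI-11". The difference in timing from EMG-2 is clear; the position of the needles is not.

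One could also say that pooling both groups (24 subjects) raises power. It does: with r = 0.5 and ρ = 0 it is about 99.7%, 94% and 65% for f = 0, 0.25 and 0.5. But the article sets its minimum per group, and a half-size sham response still leaves power far from 99%.

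**Conclusion.** The concern holds as one of sample-size justification, not of arithmetic. The 0.99 belongs to a one-treatment drop in amplitude measured elsewhere at a different time point. It is not the power of the tACP-sACP contrast, nor of any comparison of slopes. For the tACP-sACP contrast on the amplitude scale, power at 12 subjects runs from about 73-99% with an inert sham, through 49-91% with a quarter-size sham response, to 25-60% with a half-size one. These ranges assume equal SDs of change and correlations of 0 to 0.5. The article gives nothing with which to choose among them. An inert sham should not be assumed without saying so: the off-point procedure in the Acupuncture section (written there for the control group) still involves needle insertion and the same rotation schedule.

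**What to change.** Rewrite the Sample size calculation paragraph and keep 12 per group:

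1. State the test, the sidedness and the correlation or SD of change that gave 12, and say that it came from a before/after amplitude contrast in one external study.
2. Stop presenting 0.99 as the power of the trial.
3. For the tACP-sACP difference in change on the primary EMG variable, give either the detectable difference with 12 subjects (about 0.90 SD of the within-subject difference at 80% power, 1.04 SD at 90%) or power over a stated range of sham responses and correlations. If the slope is the primary variable, express this in slope units once an SD is available.
4. State that the tACP-sACP contrast will be interpreted by its estimate and confidence interval, so that a non-significant result is not taken as evidence of no effect.

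The cost is one paragraph and a less favourable stated figure. No subjects are added. The SD-unit figures do not show that 12 is adequate for the slope endpoint; they only make plain what 12 can detect.

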### Data analysis

Linear regression analysis will be applied for each individual to investigate associations between the sEMG variables and force (excluding the sixth step). The slopes of the regression lines will be used to measure the sensitivity of the sEMG variables regarding changes in force. The Shapiro-Wilk test will be used to test the normality of the data distribution regarding RMS and MDF values in the third and sixth step of the step contraction. Paired samples (Student’s t-test or Wilcoxon test) will be used to test differences between third and sixth contraction step. A mixed linear model will be used to analyze and compare the slopes of the regression lines during sustained contraction (five steps) between pre-acupuncture (EMG-1) and post-acupuncture (EMG-2) evaluations. These comparisons will demonstrate whether acupoints TE-5 and LI-11 affect the activity of the upper trapezius muscle, as hypothesized. The pain (numerical rating scale and pain area) and cervical range of motion data collected during the four evaluations will also be compared using a mixed linear model. The Statistical Package for Social Sciences (**IBM SPSS Statistics**, version 20.0, IBM™, Armonk, New York, United States) for Windows) will be employed for the statistical analysis, with the level of significance set to 5% (*P* <0.05).

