### Outcome measures

The primary outcome of the study is the EMG activity of the upper trapezius muscle after a single session of acupuncture. The secondary outcomes for the study are the numerical rating scale score for pain, pain area and cervical range of motion.

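### The trial is sized on a fall in EMG amplitude, but the only stated pre/post EMG comparison is of slopes on force; that comparison misses an equal absolute fall and does not inherit the 99% power

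*Protocol article*

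**What the plan says.** Outcome measures: "The primary outcome of the study is the EMG activity of the upper trapezius muscle after a single session of acupuncture". No summary measure is attached to it.

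Sample size calculation: the 12 per group rest on "data on the amplitude of the EMG signal in the study" of acupuncture that the article cites, namely 21.3 ± 9.5 μV before and 9.5 ± 3.5 μV after needle manipulation, with alpha 0.05 and power 0.99.

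Electromyography signal processing: "The root mean square (RMS) and median frequency (MDF) of the power spectrum will be calculated for each window". Under Experimental procedures, each recording has steps at 10, 15, 20, 25 and 30% MVC, plus a sixth step that repeats 20% MVC to look for fatigue.

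Data analysis: a regression on force is fitted for each individual, without the sixth step, and "The slopes of the regression lines will be used to measure the sensitivity of the sEMG variables regarding changes in force". EMG-1 and EMG-2 are then contrasted through those slopes in a mixed linear model. The section draws the conclusion itself: "These comparisons will demonstrate whether acupoints TE-5 and LI-11 affect the activity of the upper trapezius muscle, as hypothesized". The one other EMG test is within a recording: "Paired samples (Student’s t-test or Wilcoxon test) will be used to test differences between third and sixth contraction step".

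**The concern.** The quantity named and sized is a level of muscle activity. The quantity compared before and after acupuncture is a rate of change, that is, how steeply the EMG variable rises with force. The two can move independently. Acupuncture could lower RMS at every force level and leave the steepness as it was, and the only stated pre/post EMG contrast would not register it.

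Two things are at stake. A genuine fall in activity could be missed, although the article says this analysis will settle the EMG hypothesis. And the reader is given 99% power for an endpoint that the stated pre/post analysis does not test, with nothing from which to work out the power of the test that is planned.

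**Working it through.** **1. Reproducing the plan's figure.** Inputs from Sample size calculation: means 21.3 and 9.5 μV, SDs 9.5 and 3.5 μV, alpha 0.05, power 0.99. Difference = 21.3 − 9.5 = 11.8 μV, a fall of 11.8/21.3 = 55.4%.

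- Paired t-test, two-sided, assumed pre/post correlation 0.5: SD of the difference = √(9.5² + 3.5² − 2 × 0.5 × 9.5 × 3.5) = √69.25 = 8.32. This gives n = 12, with power 0.994.
- The correlation is not in the article. For 0, 0.25, 0.5, 0.75 and 0.9 the two-sided n is 16, 14, 12, 10 and 8.
- Two independent means, normal approximation, pooled SD √((9.5² + 3.5²)/2) = 7.16: n = 12 one-sided, 14 two-sided.

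The stated 12 is therefore reproducible, and it comes from a difference in amplitude level.

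**2. What the slope sees.** The force levels x are 10, 15, 20, 25, 30, with mean 20. The deviations are −10, −5, 0, 5, 10, and their squares sum to 250. The fitted slope is b = Σ(x − 20)y / 250.

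- *Equal absolute fall c at every step.* The change in b is −c × Σ(x − 20)/250 = −c × 0/250 = 0. This does not need RMS to be linear in force, and c may differ between people. The slope comparison is then under its null hypothesis, so power equals alpha.
- *Proportional fall to a fraction k.* The slope becomes k × b, a change of −(1 − k)b. With k = 9.5/21.3 = 0.446 and an assumed b of 1 μV per % MVC, the change is −0.55. The signal scales with b, so a variable with a shallow slope on force would show little even under a proportional fall. That could apply to MDF.
- *Third against sixth step.* Under an equal fall, (y6 − c) − (y3 − c) = y6 − y3. The fatigue test is unaffected too.

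**3. Illustration by simulation.** n = 12, 4,000 runs, paired t-tests. Assumed: mean line 1.3 + 1.0 × force (average 21.3 μV over the five steps), between-person SDs 3 (intercept) and 0.3 (slope), residual SD 2 μV.

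| Scenario | Slope test rejects | Mean-level test rejects |
|---|---|---|
| No effect | 4.8% | 5.1% |
| Equal fall of 11.8 μV | 4.9% | 100% |
| Proportional fall (× 0.446) | 100% | 100% |

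A second simulation with a smaller effect (equal fall of 6 units, between-session noise SD 4) gave 5.2% for slope and 99.5% for level. With a proportional fall of 25% the figures were 98.5% and 99.1%.

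**4. A limit on the illustration.** RMS cannot be negative. On the assumed line the 10% step averages 1.3 + 10 = 11.3 μV, and 11.3 − 11.8 = −0.5 μV. If the five steps average 21.3 μV, a full parallel fall of 11.8 requires 21.3 − 10b ≥ 11.8, so b ≤ 0.95 μV per % MVC. The 11.8 μV row therefore shows the algebra and is not a forecast. The zero in step 2 does not depend on it.

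**5. Power for the slope.** No SD or expected change for a slope appears anywhere in the article, so neither a power nor a sample size can be calculated for the planned comparison.

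**The case against.** The strongest reply is that the sized effect need not be a parallel shift. A reader might infer that the very amplitude fall the trial was sized on would be scored as no effect. The article does not support that. It gives one mean before and one after, and says nothing about how the fall is spread over force levels. Its figures lean towards scaling: if everyone fell by the same amount the between-person SD would stay at 9.5, whereas it drops to 3.5 (−63%) alongside a 55% fall in the mean; pure scaling would give 9.5 × 0.446 = 4.2. This is evidence between people, not across force levels, but it is all there is. Under a proportional fall the slope test loses almost nothing (98.5% against 99.1%). This stands, and it confines the blind spot to one form of the effect.

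Second, the slope is a deliberate choice: the Abstract says surface EMG is there to determine motor control, and slope on force is a reasonable measure of that. This also stands, and is a reason to keep the slope comparison.

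Third, the article condenses a fuller plan and does not list the model's terms, so a level effect may be in the model. It also labels no analysis as primary. One cannot therefore say that the intercept is thrown away. But the article does fix the contrast (slopes, EMG-1 against EMG-2) and the inference drawn from it, and no pre/post comparison of level is stated. That is more than missing detail.

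Fourth, a non-significant result shows absence of effect for no endpoint. True. The harm here is an effect that could be missed and a power claim attached to a different quantity.

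**Conclusion.** The concern holds in a limited form. The endpoint that carries the 99% power (EMG amplitude) is not the one in the stated pre/post comparison (slope of RMS and MDF on force). For an equal absolute fall at all five steps, the power of that comparison equals alpha, 5%, by algebra alone. For a proportional fall the RMS slope changes and the effect can be detected. The article does not say which form is expected, so the planned test is blind to one plausible form of an amplitude effect, not to every fall. In both cases the stated power does not carry over to the slope.

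The simulated rejection rates rest on assumed lines and noise, and the reproduction of 12 per group rests on an assumed correlation of 0.5 or a one-sided approximation. The invariance of the slope to an equal shift, and the absence of any slope figures in the sizing, rest on neither.

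**What to change.** In Data analysis, fit the mixed model to the step-level RMS values with force centred at 20% MVC, and test the treatment-by-evaluation effect on level. Because 20% is the average of the five force levels, this term is the effect on mean RMS over the five steps. Name it as the EMG comparison that matches the sized endpoint. Keep the existing slope comparison beside it as the motor-control measure. State the order in which level and slope are tested, so that two EMG tests do not inflate the type I error.

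In Sample size calculation, state that the 99% power refers to the amplitude comparison only. If the sponsor prefers to rely on the slope alone, the sample size would have to be re-based on an expected slope change and its SD, which the article does not supply.

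No new data are needed, since the five steps are already recorded. The cost is more than a change of wording: Trial status says recruitment is under way, so this should be a documented amendment, made before the data are analysed.

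### The fatigue check tests normality on the step values instead of the paired differences, and cannot show whether fatigue differed by treatment or recording (a minor error in a supportive analysis)

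*Protocol article*

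**What the plan says.** Under Experimental procedures, each EMG recording is a step contraction at five force levels, listed from 10 to 30% MVC, followed by one repeated level. The reason for the repeat is given there: "To investigate possible myoelectric manifestations of fatigue, a repetition of the third step (20% MVC) will be added as the sixth step".

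The Data analysis section applies Shapiro-Wilk to "test the normality of the data distribution regarding RMS and MDF values in the third and sixth step". A paired t-test or a Wilcoxon test then "will be used to test differences between third and sixth contraction step". Paired differences are not mentioned as the object of the normality test. The comparison names no treatment (tACP or sACP), no recording (EMG-1 or EMG-2) and no group.

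The effect of acupuncture on EMG is given to another analysis in the same section: a mixed linear model comparing the five-step slopes between EMG-1 and EMG-2. The sixth step is left out of those slopes. Under Outcome measures, EMG activity of the upper trapezius is the primary outcome; fatigue is not listed as an outcome.

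**The concern.** There are two separate points.

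First, the paired t-test is a one-sample test on the within-person differences, so only their distribution bears on its validity. EMG amplitude can be skewed across people while the differences within people are close to normal, and the reverse is also possible. A rule that looks at the values responds to the wrong feature in either case.

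Second, the step-3 versus step-6 contrast is the only fatigue check described. If the steps run in the listed order, fatigue builds up as force rises and can tilt the EMG-force slope. EMG-2 also follows EMG-1 in the same session. A change in slope could then reflect a change in fatigue. To weigh that explanation one must know whether the step-6 minus step-3 difference changed between recordings, and whether it did so differently under tACP and sACP. A test with no such term does not answer this. If it is run separately for each recording, it invites a reading of fatigue before but not after needling, and two separate p-values are not a comparison.

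**Working it through.** **The plan's own figure.** The article gives no figure for the fatigue test. Its sample size can be reproduced. The inputs from Sample size calculation are 21.3 ± 9.5 and 9.5 ± 3.5 μV, α = 0.05 and power 0.99.

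- δ = 21.3 − 9.5 = 11.8; SD = √((9.5² + 3.5²)/2) = 7.16; δ/SD = 1.648.
- n per group = 2(z₁₋α + z₁₋β)²/(δ/SD)². One-sided: 2(1.645 + 2.326)²/1.648² = 11.6, so 12. Two-sided: 2(1.960 + 2.326)²/1.648² = 13.5, so 14.
- A two-sided paired t-test also gives 12 if the pre/post correlation is assumed to be 0.5.

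The stated 12 is reproduced, and n = 12 is used below.

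**How skewed might the values be?** The article gives means and SDs only. If amplitude is log-normal (assumption), log-SD = √ln(1 + CV²). With CV = 9.5/21.3 = 0.45 this is 0.43; with CV = 3.5/9.5 = 0.37 it is 0.36. A log-SD of 0.6 is added as a more skewed case.

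**Two-stage rule, simulated.** There were 4,000 data sets per row, with n = 12. Between-person SD is 1, and differences are scaled by 0.3. The rule on values uses Wilcoxon if Shapiro-Wilk rejects at 0.05 for either step. The other rule tests the differences. Power is at a shift of 0.8 SD (0.8 scale units for the t distribution). All distributions are assumptions.

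| Person level / differences | Wilcoxon chosen: values vs differences | Type I error: values vs differences | Power: values vs differences |
|---|---|---|---|
| Log-normal 0.43 / normal | 0.28 vs 0.05 | 0.054 vs 0.057 | 0.70 vs 0.71 |
| Log-normal 0.6 / normal | 0.43 vs 0.05 | 0.048 vs 0.050 | 0.69 vs 0.71 |
| Normal / exponential | 0.07 vs 0.54 | 0.098 vs 0.109 | 0.88 vs 0.91 |
| Normal / t with 2 df | 0.13 vs 0.35 | 0.042 vs 0.052 | 0.36 vs 0.40 |

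- With skewed values and normal differences, the two rules reach different conclusions in about 0.5% of data sets under the null and about 2-3% under the shift.
- With skewed or heavy-tailed differences, conclusions differ in up to about 9% of data sets, and the power loss reached about 6 points in other settings tried.
- With independent noise at each step and step-3/step-6 correlations of 0.5 and 0.9, Wilcoxon is chosen by the rule on values in 14-46% of data sets with skewed levels, and in about 9% with fully normal data. The rule on differences chooses it in about 5%.

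**Separate tests by recording.** Take the same true fatigue at EMG-1 and EMG-2, with a standardized shift d in the differences. The power of a two-sided paired t-test at n = 12 is 0.47 for d = 0.6 and 0.71 for d = 0.8. If the recordings are independent, the chance that exactly one is significant is 2p(1 − p):

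- d = 0.6: 2 × 0.475 × 0.525 = 0.50.
- d = 0.8: 2 × 0.714 × 0.286 = 0.41.

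With a correlation of 0.5 between recordings, simulation gives 0.35 and 0.29. Identical fatigue would thus look different between recordings in about 30-50% of trials under these assumptions.

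**The case against.** The strongest reply is that the test does what the article asks of it. Its stated purpose is to detect fatigue. The effect of acupuncture is assigned to the slope model, and fatigue appears in neither hypothesis and in no listed outcome. A reader might infer that the plan relies on the step-3 versus step-6 test to show an effect of acupuncture, and that the test fails at this. The text does not support that reading. The sentence saying that the comparisons will show whether the acupoints affect the muscle follows the mixed-model sentence and most naturally refers to it. This part of the objection stands.

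A reader might also infer that the normality rule often leads to the wrong test and so to wrong conclusions. That is not shown. Where values are skewed and differences normal, the rule substitutes Wilcoxon, which is valid for symmetric differences. A pre-test rejection rate is not an error rate. The article gives no distribution or correlation for steps 3 and 6, and the skewness argument concerns RMS, not MDF. This stands too.

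It can also be said that the article does not describe separate tests by recording, and that stratification may be set out in a fuller document. That is fair, so the 30-50% figure describes a risk if the test is run that way. It does not describe something the plan commits to. Nor does the article make the slope analysis conditional on the fatigue result. What the objection leaves untouched is the written rule, which names the wrong quantity, and the fact that the described test cannot tell whether fatigue differed by treatment or recording.

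**Conclusion.** The point holds as a minor error in a supportive analysis. The article fixes a normality check on the step-3 and step-6 values, where the assumption concerns their differences. Under the assumed distributions this often changes which test is chosen, but seldom the conclusion. Type I error hardly differs between the two rules. With exponential differences it is near 0.10 under both, so moving the pre-test does not repair it. The power cost is about 2 points in the likelier case and up to about 6 in the less favourable ones.

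The second limb matters more. As described, the test cannot say whether fatigue differed between tACP and sACP or between EMG-1 and EMG-2, so it cannot help to exclude fatigue as an explanation for a slope change. This rests on the steps being performed in the listed ascending order, which the text implies but does not state outright. It does not mean that the plan lacks an analysis of acupuncture on EMG: the slope model is that analysis.

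**What to change.** In the Data analysis section:

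- Define the step-6 minus step-3 difference in RMS and in MDF for each person and recording.
- Drop the normality pre-test and judge the model by its residuals. At minimum, apply any normality check to the differences.
- Analyse the difference in the mixed linear model already planned, with treatment, recording and period as fixed effects and participant as a random effect. Report the tACP minus sACP contrast in the change from EMG-1 to EMG-2, with its confidence interval, and label it supportive.
- Keep a Wilcoxon test on the differences as a sensitivity analysis if wanted.

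The cost is a few sentences and slightly more analysis work. No new data are needed, because the sixth step is already part of every recording.
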